Finally, the pediatric hypertension specialist for each clinic group will track and report "time to 3rd next available appointment" for pediatric patients in their specialist clinic. This standard measure of patient access will help us understand if the hub and spoke model described above will reduce unneeded referrals to specialist clinics. The specialist will report this value on the first of every month during the baseline and intervention periods into REDCap.

Following the learning sessions in March of 2020, the study was put on hold. We are unable to continue with the original study design given the realities of pediatric care, telemedicine and the pressures put on clinics due to COVID-19 to focus on new care delivery systems that keep patients and staff safe. For that reason, we will ask a subset of already recruited Montefiore Medical Group practices to participate in a follow-up QI study examining the feasibility, acceptability and accuracy of home blood pressure monitoring (HBPM) measurements used for the confirmation of blood pressure elevation and diagnosis of hypertension. This strategy has the potential to provide a powerful new

tool for pediatricians to avoid repeated in-person BP measurements and speed time to pediatric hypertension diagnosis. We will analyze and publish data from the first year of the collaborative (November 2018-March 2020).

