
Patients over 7 years old with discordant BP categorization (e.g. normal, elevated, stage 1 or stage 2 hypertension) HBPM measurements and in-clinic BP measurements will be referred for a pediatric nephrology clinic appointment and loaned an ambulatory blood pressure monitoring device (ABPM), which is the gold standard for pediatric hypertension diagnosis. The ABPM will confirm either the HBPM or in-clinic measurement or neither. Since ABPM is not tolerated well for patients 3 to 7 years old, these patients will just be referred for a pediatric nephrology clinic appointment. In this manner, patients will receive hypertension diagnosis and more guideline compliant care. At the same time, we will be able to understand whether HBPM can be used an adjunct to in-clinic manual BP measurements.

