## **7.3 Importance of the Knowledge to be Gained**

If this study is successful, it will provide data that best-practice care delivered via QICs can reduce HTN errors in ambulatory pediatric primary care patients. It will also suggest ways to move forward to reduce or eliminate errors for other pediatric chronic conditions and improve primary and subspecialty care interactions. Based on results of this study, hospitals and accreditors/regulators may consider tracking and reporting on HTN errors in primary care pediatrics. Given the minimal risks inherent in this proposal and the large potential benefit reducing these frequent pediatric HTN errors, we believe the risks are reasonable and are outweighed by the expected benefits. Similarly, if HBPM can speed diagnosis of pediatric hypertension, and prove an accurate tool to reduce the need for clinic visits, significant changes to pediatric hypertension diagnosis will be possible and patients will benefit.

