#### K. Ambulatory Blood Pressure Monitor (ABPM)

1. Based on HBPM and Manual BP Measurements, did the patient meet the criteria to receive an ABPM and receive a nephrology referral? \*ABPM given if patient had discordant hypertension stages (e.g. normal, elevated, Stage 1 or Stage 2) between HBPM and manual BP measurements and 8 or older, all discordant patients receive nephrology referral

☐ Yes ☐ No **[STOP COMPLETING FORM]**

2. Was caregiver interested in receiving an ABPM and nephrology referral?

☐ Yes ☐ No **IF NO, STOP COMPLETING FORM**

3. Date Patient picked up ABPM (MM/DD/YYYY): \_\_/\_\_/\_\_\_\_ or ☐ N/A because patient <8 years old

4. Date Patient came for nephrology referral (MM/DD/YYYY): \_\_/\_\_/\_\_\_\_

or ☐ Not interested in nephrology referral ☐ Did not need nephrology referral

5. Date Patient started ABPM (MM/DD/YYYY): \_\_/\_\_/\_\_\_\_

6. Date Patient returned ABPM (MM/DD/YYYY): \_\_/\_\_/\_\_\_\_

7. Date ABPM summary page(s) scanned and emailed to PK and Provider: \_\_/\_\_/\_\_\_\_

8. Final diagnosis per ABPM and nephrology: \_\_\_\_\_

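### The home-monitoring phase names accuracy of HBPM as a purpose, but ABPM goes only to age-eligible children whose home and clinic categories disagree, so overall accuracy cannot be estimated

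*Protocol*

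**What the plan says.** Section 3 introduces the post-pause phase as a follow-up study "examining the feasibility, acceptability and accuracy of home blood pressure monitoring (HBPM) measurements", to be used for confirming elevation and diagnosing hypertension. Section 7.3 then says that if HBPM can speed diagnosis and "prove an accurate tool to reduce the need for clinic visits", significant changes to pediatric hypertension diagnosis will become possible.

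Section 3 calls ABPM the device "which is the gold standard for pediatric hypertension diagnosis". It offers ABPM to "Patients over 7 years old with discordant BP categorization" between HBPM and clinic measurements, and states its use: "The ABPM will confirm either the HBPM or in-clinic measurement or neither". Younger children are referred to nephrology without ABPM. Section K of the BP-CATCH 2.0 Chart Review Tool applies the same gate. If the criteria are not met, the form stops there, so concordant children have no ABPM result.

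The formal aim and analyses are narrower than the word accuracy. Aim 4 (Section 2) covers feasibility and correlation with clinic readings. The outcome paragraph after Table 2 makes feasibility and acceptance primary and lists concordance. Section 6.1 plans descriptive statistics and concordance. Section 6.3 calls the phase a pilot with no prior power analysis.

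**The concern.** Accuracy means agreement with the truth, for which the protocol's stand-in is ABPM. That stand-in is withheld whenever the two methods agree. A child whom HBPM and clinic readings both place in the same wrong category looks like a success in the concordance analysis and never reaches ABPM. Agreement with clinic readings cannot fill the gap, because they are not the reference.

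At stake is what the phase may conclude. Section 1.2 notes that current guidelines do not endorse HBPM for diagnosis because evidence is insufficient. An accuracy statement from this phase would speak to that open question without the data to support it. A later analysis plan cannot repair this, since the reference result is not collected in concordant children.

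**Working it through.** The protocol gives no accuracy figure, discordance rate or power calculation for this phase, so there is nothing to reproduce. The check is whether the planned data determine accuracy.

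**Set-up, within ABPM-eligible ages, taking ABPM as correct, as the protocol does.**
- *d*: share of children with discordant categories (not in the documents; assumed 20% to 50%).
- *h*, *c*, *n*: among discordant children, the shares in whom ABPM agrees with HBPM, with clinic BP, or with neither; *h* + *c* + *n* = 1. All three are observed if discordant children take up ABPM.
- *q*: share of concordant children whose shared category is right. Never observed.

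Overall HBPM accuracy = *d·h* + (1 − *d*)·*q*.

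As *q* may lie anywhere from 0 to 1, accuracy lies between *d·h* and *d·h* + (1 − *d*). The width is 1 − *d*, and sample size does not enter. This holds for the protocol's four categories.

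| *d* | *h* = 0.3 | *h* = 0.5 | *h* = 0.7 |
|---|---|---|---|
| 0.20 | 0.06–0.86 | 0.10–0.90 | 0.14–0.94 |
| 0.30 | 0.09–0.79 | 0.15–0.85 | 0.21–0.91 |
| 0.50 | 0.15–0.65 | 0.25–0.75 | 0.35–0.85 |

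**Sensitivity and specificity.** These need a yes/no split, so this illustration reduces the categories to hypertension present or absent. Take 100 children, 30 of them discordant, with the same verified results throughout:
- HBPM positive and clinic negative: 6 (3 with hypertension, 3 without).
- HBPM negative and clinic positive: 24 (8 with, 16 without).

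Only the unseen truth in the 70 concordant children (30 both positive, 40 both negative) is varied:

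| Case | Both positive: with / without | Both negative: with / without | HBPM sensitivity | HBPM specificity | HBPM accuracy | Clinic accuracy |
|---|---|---|---|---|---|---|
| A | 28 / 2 | 2 / 38 | 31/41 = 0.76 | 54/59 = 0.92 | 0.85 | 0.77 |
| B | 15 / 15 | 10 / 30 | 18/36 = 0.50 | 46/64 = 0.72 | 0.64 | 0.56 |
| C | 5 / 25 | 20 / 20 | 8/36 = 0.22 | 36/64 = 0.56 | 0.44 | 0.36 |

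The study would see identical data in all three cases. From verified children alone, HBPM sensitivity would be 3/11 = 0.27 and specificity 16/19 = 0.84 each time.

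**What is identified.** Clinic accuracy is *d·c* + (1 − *d*)·*q*. Subtracting, the *q* term cancels, and HBPM minus clinic = *d*(*h* − *c*). In the tables this is 0.30 × (19/30 − 11/30) = 0.08 in every case.

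**Age wording.** Section 3 uses "Patients over 7 years old with discordant BP categorization" and gives as its reason "Since ABPM is not tolerated well for patients 3 to 7 years old". The form uses "between HBPM and manual BP measurements and 8 or older, all discordant patients receive nephrology referral" and offers the box "N/A because patient <8 years old". Age is charted to the nearest half year. At a charted 7.0 or below, and at 8.0 or above, the two agree. At a charted 7.5, over 7 is true and 8 or older is false.

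**The case against.** The strongest reply is that no accuracy analysis is planned. Aim 4, the outcome list and Section 6.1 stop at feasibility, correlation and concordance. Section 7.3 is conditional and describes why the knowledge matters; it is not an objective. The ABPM paragraph gives ABPM a clinical role and concludes only that HBPM may be an adjunct. Its either-or-neither sentence already describes a legitimate tabulation. All of this stands, and it confines the point to the accuracy wording in Sections 3 and 7.3. It does not remove the point: Section 3 states accuracy for confirmation and diagnosis as a purpose that the data cannot serve.

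Stronger readings are tempting but are not supported:
- A reader might infer that the protocol undertakes to show HBPM can replace clinic visits. Section 7.3 speaks only of reducing the need for them, and within an if-clause.
- A reader might infer that every ABPM-based comparison is distorted. Concordant pairs cancel from the difference between methods, so the relative comparison in ABPM-eligible children is sound.
- A reader might infer that every child misclassified by both methods is missed. With four categories, children wrong on both but in different categories are discordant and, if age-eligible, are offered ABPM. Only errors into the same category go unseen.
- A reader might call the age limits a flat contradiction. In completed years, as in the consent bands of Section 3 (3–6, 7–17, 18–22), over 7 and 8 or older coincide. They part only for a child between 7 and 8 when fractional age is used.

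**Conclusion.** The point holds in limited form. With ABPM confined to discordant, age-eligible children, overall accuracy, sensitivity and specificity of HBPM are not identified. The uncertainty about overall accuracy is 1 minus the discordance rate: 0.80, 0.70 or 0.50 at assumed discordance of 20%, 30% or 50%. More patients would not narrow it. Over the whole 3 to 22 age range the unverified share is larger still, because younger discordant children have no ABPM either.

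The discordance rates and the constructed tables are assumptions; the structural result does not depend on them. Feasibility and acceptance, which are primary for this phase, are unaffected. HBPM-clinic concordance is also supported, as is the relative comparison among ABPM-eligible children, provided discordant families take up ABPM, which the form lets them decline. The age wording is a minor, separate matter of clarity.

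**What to change.** In Section 3 and Section 7.3, replace the references to accuracy and to an accurate tool with agreement between HBPM and clinic readings. State that ABPM results will be reported only as the proportions of discordant, age-eligible children in whom ABPM agreed with HBPM, with the clinic reading, or with neither. Add that no overall accuracy, sensitivity or specificity of HBPM will be claimed.

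Separately, reconcile the ABPM age wording between Section 3 and section K of the chart review tool, and say whether completed years or charted half-years apply. Which limit is right is for the investigators.

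The cost is a few sentences in the protocol and form, with no extra measurements. The drawback is a narrower conclusion for this phase.

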#### 4. Pediatric HTN Outcome Measures:

The research team has developed clearly defined primary and secondary outcome measures for pediatric HTN diagnosis and management errors, and has experience using evidence-based tools for their improvement. All outcome measures are described in Table 2. **Error! Reference source not found.** These measures will be compared between usual care, QIC without subspecialist involvement, QIC with subspecialist involvement, and hub and spoke QIC. The primary outcome is pediatric HTN or EBP diagnosis and management errors, defined as the number of patients with an elevated systolic or diastolic BP for age, sex and height (defined as  $\geq 90^{\text{th}}$  percentile for age, sex and height or  $>120/80$ , whichever is lower, in  $\geq 3$  year old patients) who did not have all correct diagnostic

and management decisions completed per 100 patients with an elevated BP measured across all 3 intervention conditions versus usual care (control) condition. Each practice site will identify the first 10 patients seen in their site monthly with an elevated BP and then evaluate those patients following the elevated BP to confirm correct HTN and EBP diagnosis and management steps. During the baseline period, this number will be 17 patients per month for 3 months, in order to provide an adequate baseline sample for practices to begin changing their practice. For example, if a patient already had one elevated BP reading in the Stage 1 HTN range and then presented for care, the practice site would record if they 1) received a repeat BP measurement in 1-2 weeks, 2) four extremity BP measurements and 3) a scheduled appointment for a repeat BP measurement in 3 months, etc... Similarly, if a patient already had 3 BPs in the Stage 1 HTN range and then presented to the practice site, this measure would track whether they received 1) all appropriate laboratory testing, 2) a subspecialist referral, and if diagnosed with HTN, 3) management with a recommended antihypertensive medication. In this way practice sites will be able to feasibly collect data, receive real-time and actionable data feedback, and work to reduce harmful errors. We acknowledge that HTN error measurement in the control period may introduce an intervention effect, but we have no reason to believe this effect will be different between the intervention and control practices.

As Secondary Outcome Measures, we will also track each of these markers of correct care individually and the time to completion from initial elevated BP measurement to each marker. This allows us to investigate how the different QIC conditions affect the proportion of patients who receive guideline recommended care, which diagnostic and management steps are correctly implemented, and the time it takes for patients to receive this care. We can then test error rate and time to care improvement between usual care, the QIC without subspecialist involvement, the QIC with subspecialist involvement, and the hub and spoke model QIC.

In order to confirm appropriate screening, practices will perform anonymous self-audits on the 5 most important aspects of BP measurement (a. choosing children to screen as per 2017 guideline recommendations; b. positioning and calming a child for BP measurement; c. choosing an appropriately sized BP cuff; d. inflating the cuff to the appropriate pressure, and e. documenting percentiles and interpreting when the BP is elevated based on cumbersome age, sex and height tables) during the first 6 months of the project: either the initial local QIC without subspecialist involvement or during the baseline collection period for the control group. This anonymous self-audit will occur weekly for each person who shares primary responsibility for measuring pediatric blood pressures at triage. These data will be submitted anonymously into REDCap.

Finally, as noted above, we will compare time to 3rd next available appointment for pediatric patients to subspecialist clinics in order to assess the effects of pediatric primary care providers referring and managing different types of patients with hypertension.

| Primary Outcome Measure    | Number of patients without all correct diagnostic and management decisions (Figure 4) per 100 patients with measured elevated BP                                                                                                                                                                                                                                                                                                                                                                                                                                                                                                                                                                                                                                                                                                                                                                                                                         |
|----------------------------|----------------------------------------------------------------------------------------------------------------------------------------------------------------------------------------------------------------------------------------------------------------------------------------------------------------------------------------------------------------------------------------------------------------------------------------------------------------------------------------------------------------------------------------------------------------------------------------------------------------------------------------------------------------------------------------------------------------------------------------------------------------------------------------------------------------------------------------------------------------------------------------------------------------------------------------------------------|
| Secondary Outcome Measures | 
 
1. Number of patients without correct diagnostic and management decisions at specified points per 100 patients with measured elevated BP 
 
a. Re-measuring BP twice in clinic via auscultation
 
b. Weight and nutrition counseling
 
c. Repeat BP measurement visits appropriately timed
 
d. Initial laboratory workup
 
e. Subspecialist referral
 
f. Definitive medication management initiation
 
 
 
2. Mean time from first elevated BP to specific points in diagnostic and management process (see #1 above)
 
3. Number of BPs measured correctly with appropriately screened patient, patient position, cuff size, inflation, BP percentiles correctly documented and interpreted per 100 observations conducted
 
4. Time to 3rd next available subspecialist appointment
 
 |

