## 2. Study Aims:

We propose to conduct a multisite, prospective, cluster-randomized trial, broadening and deepening our prior work on recognition of pediatric elevated BP, which will test methodologies to ensure every pediatric patient is screened, and if HTN or EBP are present, diagnosed and managed appropriately and expeditiously. This design, with practices randomized in a stepped-wedge fashion to a HTN QIC a) without subspecialist involvement, b) with subspecialist involvement and c) with pediatrician HTN diagnosis and management and subspecialist back-up, will also serve as a test case for whether pediatricians can diagnose and manage common chronic conditions (e.g., HTN) with a supporting subspecialist advisor. This proposal responds to AHRQ's Funding Opportunity Announcement PA-15-339, designed to develop evidence to improve safety in ambulatory care settings. This work is one of the first to test implementation of the new 2017 pediatric HTN guidelines and focuses on children in rural and urban settings, AHRQ priority populations.

Specific Aim 1: Determine whether a QIC in a national group of at least 60 pediatric practices, building on our prior elevated BP recognition work, is associated with reduction of errors in the broader outcomes of 1) HTN diagnosis, 2) initiation of management, and 3) time to diagnosis and management.

*Hypothesis 1: Practices randomized to a QIC will experience a 50% reduction in pediatric HTN and EBP diagnosis and management errors as compared to usual care.*

Specific Aim 2: Investigate whether a QIC with relevant, local pediatric HTN subspecialist involvement improves diagnosis and management for children with HTN.

*Hypothesis 2: Practices randomized to a collaborative with relevant, local HTN subspecialist involvement following participation in the original QIC, will experience an additional 15% reduction in pediatric HTN and EBP diagnosis and management errors as compared to the original QIC.*

Specific Aim 3: Determine whether pediatrician co-diagnosis and co-management of HTN, conducted via a 'hub and spoke' model where one pediatric HTN subspecialist advises multiple primary care pediatricians, improves diagnosis and management for children with HTN.

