**Table 2: Primary and Secondary Outcome Measures**

## 5.

The primary outcome for the new phase of the study will be the feasibility and acceptance of HBPM by families of children with one elevated BP measurement. We will measure feasibility of HBPM by investigating 1) the percent of patients who were not interested in receiving the HBPM device, 2) the percent of patients who did not return any data on the HBPM measurements, 3) the percent of patients completing all requested measurements and the percent completing at least half

of the requested measurements, 4) the days between agreeing to come in for the device, to when they received the HBPM and when data was returned (actual dates will only be visible to the Honest Broker), and 4) the concordance between HBPM, and manual in-clinic BP measurements, and 5) percent of children diagnosed with hypertension. For those patients contacted for HBPM, we will continue to track the above pre-COVID outcomes as well. No data described above will be collected on patients not identified for this new phase of the study at this time.

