#### Exclusion Criteria for Initial Visit:

- Prior hypertension/elevated BP diagnosis. NOTE: Patient can have prior elevated BP measurements as long as no diagnosis has been made
- $\text{BP} \geq 95^{\text{th}}$  percentile + 30mm or  $>180/120$  or symptomatic patient
- Prior diagnosis of congenital heart disease, chronic kidney disease, urologic disease (e.g. posterior urethral valve, vesicoureteral reflux) or organ transplant,
- Previously included in BP-CATCH data entry
- Acute care visit (e.g., fever, viral illness, asthma attack, pain in any body part, etc.)

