### **Protected Health Information to be held by an “Honest Broker”:**

Our project team needs to know how many days elapsed between certain dates (e.g. number of days between initial visit and sending laboratory studies). In order to avoid making each practice count the number of days elapsed between the initial visit date and other dates (could be over 400 days), and to avoid submitting PHI to the research team, we are using an IRB approved “Honest Broker” technique. This means that practices will enter specific visit dates into REDCap, but these dates will NEVER be given to the research team and will be kept in a separate database. The research team will only have access to days elapsed between visits which is provided to them from the Honest Broker. The Honest Broker for this project is [name], Lead Bioinformatics Analyst, Research Informatics Core (RIC), Albert Einstein College of Medicine; [name] [contact].

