**B. How Many Elevated BPs at Unique Visits in the Last 24 Months?**

1. In the last 24 months, at healthcare maintenance and/or non-acute care visits, how many elevated BPs did the patient have at unique visits? Please count total number of unique visits with abnormal BPs and no normal BPs at those visits in the last 24 months at a healthcare maintenance or non-acute care visits and check appropriate box

**Note:** A patient may also have one or more normal BPs at separate unique visits in the last 24 months at healthcare maintenance or non-acute care visits and be included.

- ☐ This visit is their **First elevated BP** [Go to Section C]  
☐ This visit is their **Second elevated BP** [Go to Section D]  
☐ This visit is their **Third elevated BP** [Go to Section E]  
☐ This visit is their **Fourth or more elevated BPs** [Go to Section E]  
☐ This visit is their first visit to this clinic or in our EHR. Therefore, this visit is their **First elevated BP** [Go to Section C]

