**E. Third Elevated BP in last 24 months at healthcare maintenance or non-acute care visit**

If this is the initial visit which qualifies a patient for BP-CATCH, this must be a healthcare maintenance or non-acute care visit. If this patient previously had a qualifying BP-CATCH elevated BP visit above, then this can be any visit when the patient returned for BP follow-up.

1. Date of visit with third or more elevated BP noted (MM/DD/YYYY): \_\_/\_\_/\_\_\_\_ [THESE DATA ARE ENTERED INTO REDCAP BUT NOT GIVEN TO RESEARCH TEAM]

1a. Height at this visit with an elevated blood pressure \_\_\_\_\_ (centimeters) ☐ Not done at this visit

1b. Weight at this visit with an elevated blood pressure \_\_\_\_\_ (kilograms) ☐ Not done at this visit

2. Systolic Blood Pressure: \_\_\_\_\_ Systolic Percentile: \_\_\_\_\_ ☐ Percentile unknown

3. Diastolic Blood Pressure: \_\_\_\_\_ Diastolic Percentile: \_\_\_\_\_ ☐ Percentile unknown

4. Blood pressure measured by: ☐ Automated (Oscillometry) [Go to 4a] ☐ Manual (Auscultation) [Go to 4c]

4a. Was this BP repeated by manual (auscultation)? ☐ Yes [Go to 4b] ☐ No [Go to 4a.i.]

4a.i. Was automated BP still elevated ( $\geq$  90th percentile for patient's height, weight and sex, or  $\geq 120/80$ )?

☐ No [STOP COMPLETING FORM]

☐ Yes ( $\geq$  90th percentile for patient's height, weight and sex, or  $\geq 120/80$ ) [Go to 5]

4b. What were manual BP results:

Systolic Blood Pressure: \_\_\_\_\_

Diastolic Blood Pressure: \_\_\_\_\_

4c. Was BP re-measured again with manual ?

☐ Yes [Go to 4c.i] ☐ No [Go to 4e]

4c.i. If Yes, what were additional results: Systolic Blood Pressure #2: \_\_\_\_\_

Diastolic Blood Pressure #2: \_\_\_\_\_ [Go to 4d]

4d. Was average of 2 manual BPs still elevated ( $\geq$  90th percentile for patient's height, weight and sex, or  $\geq 120/80$ )?

☐ Yes [Go to 5] ☐ No [STOP COMPLETING FORM]

4e. Was first manual BP elevated ( $\geq$  90th percentile for patient's height, weight and sex, or  $\geq 120/80$ )?

☐ Yes [Go to 5] ☐ No [STOP COMPLETING FORM]

5. Did provider document that the following were discussed with patient and/or family:

5a. Weight counseling ☐ Yes ☐ No ☐ N/a patient has normal BMI

5b. Nutrition counseling ☐ Yes ☐ No

5c. Lifestyle modifications ☐ Yes ☐ No

6. Did the patient have BP in Stage II Hypertension range ( $\geq 95$ th+12mm to <95th+30mm; or  $\geq 140/90$  to <180/120)?

☐ Yes [Go to 6a] ☐ No [Go to 7]

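### Time from first elevated BP cannot be computed as defined for children who enter at a second or later elevation, because the chart tool never asks them for that date

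*Protocol*

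**What the plan says.** Aim 1 (protocol, section 2) lists "3) time to diagnosis and management" among its outcomes but names no starting point. Section 4 supplies one. Its text promises "the time to completion from initial elevated BP measurement to each marker", and Table 2, secondary outcome 2, gives "Mean time from first elevated BP to specific points in diagnostic and management process (see #1 above". The points referred to are re-measurement, counseling, repeat visits, laboratory work-up, referral and start of medication.

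The exclusion criteria in the Data Collection Guidance admit children with a history of elevated readings: "Patient can have prior elevated BP measurements as long as no diagnosis has been made". Section B of the Chart Review Tool asks, over the last 24 months, "how many elevated BPs did the patient have at unique visits", and uses the answer to choose the section where the form starts. Section C asks for the date of the first elevation. Section D asks for the date of the second. Section E, item 1, asks for "Date of visit with third or more elevated BP noted".

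The honest-broker text in the same appendix explains that sites should not have to "count the number of days elapsed between the initial visit date and other dates (could be over 400 days".

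For the home blood pressure monitoring (HBPM) phase, section 5 lists as a feasibility measure "the days between agreeing to come in for the device, to when they received the HBPM and when data was returned".

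**The concern.** A time outcome needs its starting date. Section 4 starts the clock at the first elevated reading, but the form collects that date only from children who happen to enter at their first elevation. A site that enters a child at the third elevation has just looked back over the chart to count the earlier ones, and is then asked for none of their dates.

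Two things can follow. Under the Table 2 definition these children have no usable time and drop out. If the qualifying visit is used in their place, their times are too short, and a change in the share of late entrants from one condition to another would change the mean time with no change in care. An analysis plan can choose between these two treatments, but it cannot restore a date that was not collected.

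**Working it through.** The protocol states no figure to reproduce here. The check is a trace of the form, followed by an illustration of size.

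**Trace of the entry routes (Chart Review Tool, Sections B to G)**

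| Answer in Section B | Form starts at | Reaches the first-elevation date (C, item 1)? |
|---|---|---|
| First elevation | C | Yes |
| First visit to the clinic or EHR | C | Yes |
| Second elevation | D | No |
| Third elevation | E | No |
| Fourth or more | E | No |

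Sections F and G ask for dates of laboratory, imaging, referral, specialist, echocardiogram and medication events. They do not return to Section C. Three of the five routes therefore lack the starting date.

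**Largest possible delay.** The look-back is 24 months. At 365.25/12 = 30.44 days per month, 24 × 30.44 ≈ 730 days between the first elevation counted and the qualifying visit.

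**Effect on a mean, if the qualifying visit replaces the first elevation.** Let p be the share of late entrants among children who have a time for the marker in question, and L their mean lost interval. The mean is understated by p × L. The documents give neither p nor L, so these values are assumptions:

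- p = 10%, L = 3 months: 0.10 × 3 × 30.44 ≈ 9 days
- p = 20%, L = 6 months: 0.20 × 6 × 30.44 ≈ 37 days
- p = 20%, L = 12 months: 0.20 × 12 × 30.44 ≈ 73 days
- p = 50%, L = 12 months: 0.50 × 12 × 30.44 ≈ 183 days

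**Effect on a comparison of conditions.** The bias in a difference of two means is p₁L₁ − p₀L₀, in favor of the condition with more late entrants. If p and L are the same in both conditions, it is zero. With a common L it is (p₁ − p₀) × L:

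| Difference in share | L = 6 months | L = 12 months |
|---|---|---|
| 0 points | 0 days | 0 days |
| 5 points | 9 days | 18 days |
| 10 points | 18 days | 37 days |
| 20 points | 37 days | 73 days |

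**HBPM form (BP-CATCH 2.0 Chart Review Tool).** Section H records the number of call attempts, whether contact was made, whether the family was interested, and the clinic visit date. Section J records the dates of receiving the device, starting to use it, and the clinic receiving the data. The interval from receipt to return can be computed. The interval from agreement to receipt cannot, because no field holds the date of agreement.

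**The case against.** **The late clock is an inference.** The honest-broker text gives elapsed days from the initial visit as an example. No section says that Section D and E entrants will be analyzed from the qualifying visit under the first-elevation label. Under Table 2 as written they simply have no time. This stands, and the point is therefore put as two alternatives. Neither delivers the outcome as defined.

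**A common delay largely cancels.** Section 4 plans comparisons between conditions. If late entrants are equally frequent and equally late in each, a difference in means is unaffected. This stands. Only a shift in entry stage biases the comparison, and the documents do not show whether one occurs.

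**Stronger readings that the documents do not support.** A reader might infer that a child diagnosed at a third-elevation entry visit is stored with 0 days to diagnosis. The tool has no date-of-diagnosis field, only yes/no items about the visit, and diagnosis is not among the points listed in Table 2. A reader might also set the assumed understatements beside the 46-day preliminary mean in section 1.3 and conclude that the error is as large as the outcome. A true mean of 46 days could not be understated by 73, and the shares and delays are assumed.

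**Collection has mostly ended.** The collaborative was paused in March 2020, and section 5 rules out further collection outside the HBPM group. New fields would come too late for most charts. This also stands, and it makes the analysis remedy the main one.

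**The missing date has drawbacks of its own.** Phases last six months and the look-back is 24, so counting from the look-back date charges delay that predates a condition to that condition. Because a prior diagnosis is an exclusion, that earlier time is also free of diagnosis by construction.

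**The HBPM date may exist elsewhere.** The data and safety monitoring section says that time from phone contact will be collected, and one coordinator takes consent by phone. A consent record may hold the date, but Section H does not.

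**Conclusion.** The point holds as a mismatch between a secondary outcome and the form that feeds it. For children who enter at the second, third, or fourth-or-later elevation, time from first elevated BP cannot be computed as defined. Counting from the qualifying visit would start their clock late by anything up to about 24 months.

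The size of any bias is not known. The figures above rest on assumed shares and delays. A biased comparison also requires the entry-stage mix, or the delay, to differ between conditions. The primary outcome, the proportion of children without fully correct care, does not use this date. The matter should be settled before the first-year data are reported, but it does not threaten the trial's main result.

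The HBPM gap is separate and smaller: one stated interval has no recorded start on its form.

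**What to change.** 1. **Analysis.** Restrict time from first elevated BP to children who entered through Section C. The label should say that first means first in the 24-month look-back, as Section C does. Report Section D and E entrants separately as time from the qualifying visit, stratified by the entry stage in Section B. Show the entry-stage mix by condition. No new data are needed. The cost is fewer children in the first analysis. Because section 1.2 reports that over 75% of patients did not return on time for a second or third reading, the loss may be heaviest for the later markers.
2. **Data, where still possible.** For charts still being collected or open to re-query, record the date of the first elevated visit in the look-back window and have the honest broker compute days from it. This costs one date per chart, though a re-query across the 64 consented practices may not be practical. Present that analysis with the caution that part of the interval may predate the condition.
3. **HBPM form.** Add to Section H the date on which the family agreed to come in, or link it from the phone-consent record through the honest broker. This costs one field or one link.
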